### Randomization

Participants are allocated sequentially to either the intervention or the control group using a randomization list constructed by block randomization with variable block size. Randomization is furthermore stratified on: (a) sex and (b) the ability to perform active finger extension at baseline; active finger extension has shown to be a simple and reliable early predictor of recovery of upper limb functioning in stroke patients [9, 54]. The randomization sequence was generated with the random generator in SAS. The randomization list is kept by administrative personnel and concealed from the other project investigators, with the exception of SPM. Allocations are performed after baseline assessments by contacting the administrative personnel who forwards the group allocation to the personnel responsible for ESS/sham ESS treatment. SPM is occasionally involved in performance of group allocation in the absence of the administrative personnel.

### Blinding

Although complete blinding of the participants to the group allocation is impossible because of the nature of the ESS treatment (i.e., participants can feel the stimulation and are aware of whether it is delivered in continuous or intermittent sham mode), participants are kept unaware of how it is supposed to feel. The personnel who apply ESS are not blinded to the group allocation, and they also collect data from medical records that will be used to characterize the sample. The therapists providing usual rehabilitation as well as other personnel involved in usual patient care are blinded to the group allocation. Investigators who perform outcome assessments and data analysis are unaware of the group allocation, with the exception of the principal investigator (SPM) who is involved in group allocation in the absence of the administrative personnel, who are normally responsible for the group allocation and not involved in any other trial procedures. For further details see Table 1.

### Statistical analysis

Background characteristics will be compared between the intervention groups with *t* tests (continuous variables) or chi-squared tests (categorical variables). The development of both primary and secondary outcome variables will be analyzed in longitudinal models over the stroke recovery trajectory (baseline, post-intervention and 6-month follow-up), and the difference of the outcomes between the two intervention groups at each of the study time points will be analyzed in multivariable linear regression models. Analyses will be adjusted for the stratification variables (sex and the ability to perform finger extension). Possible differential attrition is adjusted for by weighting the outcomes that are available at each of the study time points with the inverse of the probability of being present; these probabilities are estimated in logistic regression models including all background characteristics and outcomes at previous study time points. To account for this weighting and for repeated observations on the same individual generalized estimating equations (GEE) methods are used to adjust the variance of the parameter estimates. Analyses are performed with SAS version 9.4. The statistical significance level is 5%.

Additional file 3 shows the SPIRIT Checklist [55, 56] for this study protocol.

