**Methods/design:**

A sample of 102 patients with upper limb paresis of varying degrees of severity is assigned to either the intervention or the control group using stratified random sampling. The intervention group receives ESS plus usual rehabilitation and the control group receives sham ESS plus usual rehabilitation. The intervention is applied as 1 h of ESS/sham ESS daily, followed by motor training of the affected upper limb. The ESS/sham ESS treatment is initiated within 7 days from stroke onset and it is delivered during hospitalization, but no longer than 4 weeks post stroke. The primary outcome is hand dexterity assessed by the Box and Block Test; secondary outcomes are the Fugl-Meyer Assessment, hand grip strength, pinch strength, perceptual threshold of touch, degree of pain, and modified Rankin Scale score. Outcome measurements are conducted at baseline, post intervention and at 6-month follow-up.

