## Methods/design

### Trial design

This study is conducted as a single-blinded randomized controlled trial with two arms and blinded endpoint adjudication. The intervention consists of ESS/sham ESS treatment immediately followed by training of the affected upper limb in addition to usual rehabilitation. The ESS/sham ESS treatment is initiated within the first 7 days post stroke. The first 4 weeks post stroke seem to be crucial for gaining maximal recovery of upper limb functioning [9, 10]. Since it is not possible for us to continue the intervention after hospital discharge for financial and logistical reasons, we decided to investigate the effect of our intervention during hospital stay (mean hospital stay when designing this study: 21 days), but no longer than 4 weeks post stroke. Outcome measures are assessed at three time points: (1) within the first 7 days post stroke prior to intervention onset (baseline), (2) at hospital discharge or 4 weeks post stroke (post-intervention) and (3) at 6 months post stroke (follow-up), which is the time point where the recovery of upper limb functioning is expected to level off [12–14]. Figure 1 shows the SPIRIT flow diagram of the trial.

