### Outcome measures

The primary outcome measure is the Box and Block test (BBT) at 6 months post stroke. The BBT assesses the upper limb’s capacity to perform reaching, grasping, moving and releasing objects unilaterally [40]. These motor skills are essential components of performing ADLs and, therefore, of relevance when evaluating whether our intervention contributes to achieving the ultimate goal of rehabilitation: independence in daily life. Normative data are available for the healthy adult population [40], and the instrument has been validated for use in stroke patients [41].

The secondary outcomes measures are: (1) the upper extremity section of the Fugl-Meyer Assessment (FMA-UE) [42–44], (2) hand-grip strength [45], (3) palmar, lateral and thumb-to-index pinch strength [45], (4) perceptual threshold of touch [46, 47], (5) pain in the upper limb during performance of the BBT using Numerical Rating Scale-11 [48] and (6) the mRS score [49, 50]. The FMA-UE, hand-grip strength, pinch strength, perceptual threshold of touch, and degree of pain are ways to quantify the level of motor and sensory impairments in the upper limb. The mRS is a clinician-reported measure of global disability which is widely used as an endpoint in stroke trials.

All outcome measurements are carried out by EG. Baseline assessments are performed at the stroke unit. Post-intervention and 6-month follow-up assessments are performed at the stroke unit, the patient’s home, or the inpatient rehabilitation center or nursing home, depending on the residence of the participant at the scheduled time.

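### The 6-month BBT comparison does not name baseline BBT as a covariate, which gives up precision at no saving

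*Protocol article*

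**What the plan says.** The endpoint is fixed under Outcome measures: "The primary outcome measure is the Box and Block test (BBT) at 6 months post stroke".

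The baseline value exists for every patient assessed. The abstract states "Outcome measurements are conducted at baseline, post intervention and at 6-month follow-up", and Trial design places the first assessment "within the first 7 days post stroke prior to intervention onset (baseline"). The Randomization section puts allocation after the baseline assessments, so baseline BBT is a valid pre-randomization covariate.

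The Statistical analysis section makes four relevant statements:

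- Between-group comparison: "the difference of the outcomes between the two intervention groups at each of the study time points will be analyzed in multivariable linear regression models".
- Adjustment set: "Analyses will be adjusted for the stratification variables (sex and the ability to perform finger extension"). No other covariate is named.
- Trajectory: outcomes "will be analyzed in longitudinal models over the stroke recovery trajectory (baseline, post-intervention and 6-month follow-up"), so baseline is one of the responses.
- Attrition weights: "these probabilities are estimated in logistic regression models including all background characteristics and outcomes at previous study time points". Earlier outcome values therefore help to predict who is still present.

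**The concern.** The trial deliberately admits all degrees of upper limb paresis (any FMA upper limb score below 66), and its Discussion expects difficulty in detecting an effect in so mixed a sample. Much of the spread in 6-month BBT may already be visible at entry. A model that conditions on the entry score removes that part from the error term and corrects for chance imbalance in it. A model with only two yes/no factors does so only as far as those factors carry the same information. The protocol accepts the principle, since it stratifies on and adjusts for finger extension as an early predictor of recovery. It then stops short of the baseline value of the outcome itself. What is at stake is the width of the confidence interval for the primary result, and likewise for each secondary outcome.

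**Working it through.** **Number of completers.** The protocol starts from 37 per group and allows for 8% deaths and 20% other loss: 37 / (0.92 × 0.80) = 50.3, rounded up to 51. The stated 51 per group reproduces, so 37 completers per arm is the planning case below.

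**Does the repeated-outcome model already use baseline?** This was simulated with 37 per arm, three visits and complete data. The assumptions were a residual SD of 12 and correlations given the stratifiers of 0.7 (baseline to post-intervention), 0.6 (baseline to 6 months) and 0.8 (post-intervention to 6 months). Empirical SE of the 6-month contrast over 200 runs:

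| Analysis | SE |
|---|---|
| Regression at 6 months on group, sex, finger extension | 2.93 |
| GEE, baseline as a response, free group effect at each visit | 2.93 |
| GEE, contrast of change from baseline | 2.69 |
| GEE, common baseline mean in both arms | 2.41 |
| ANCOVA, baseline BBT added | 2.40 |

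The first two rows gave the same estimate in every run (differences below 1e-13). With a free group effect at each visit, entering baseline as an outcome adds nothing to the 6-month comparison.

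**Do the attrition weights use it?** They were not simulated, but the argument is structural. With no dropout every weight is 1 and baseline BBT has no part in the 6-month contrast. With dropout the weights make those present resemble those randomized. They do not remove the spread at entry, or a chance imbalance at entry, in that randomized sample.

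**Size of the gain.** Let ρ be the partial correlation of baseline with 6-month BBT after sex and finger extension. The protocol does not give it, so the values are assumptions. Adding baseline multiplies the variance by (1 − ρ²), so the reduction is ρ². The SE is multiplied by √(1 − ρ²), and 37 completers are worth 37 / (1 − ρ²).

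| ρ | Variance reduction | SE factor | 37 completers worth |
|---|---|---|---|
| 0.3 | 9% | 0.95 | 40.7 |
| 0.5 | 25% | 0.87 | 49.3 |
| 0.7 | 49% | 0.71 | 72.5 |

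**How much does finger extension already carry?** Suppose baseline severity is normal, finger extension splits it at the median, and r is the plain correlation of baseline with 6-month BBT. Within each half the baseline variance is 1 − 2/π = 0.363 of the whole, so ρ² = 0.363r² / (0.363r² + 1 − r²).

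- r = 0.5: 0.091 / 0.841 = 11% (ρ = 0.33)
- r = 0.7: 0.178 / 0.688 = 26% (ρ = 0.51)
- r = 0.8: 0.233 / 0.593 = 39% (ρ = 0.63)

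**Floor.** A further simulation used 74 patients, stratified allocation and 40–60% with finger extension. Baseline BBT was set to zero in those without extension, with a 15% floor at 6 months. The variance reduction fell to about 3–8%, 10–23% and 17–32% for r = 0.5, 0.7 and 0.8, where r is the correlation before flooring. All of these settings are assumptions.

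**The case against.** The strongest reply is that nothing here is invalid. Randomization is stratified on sex and finger extension and both are in the model, so the planned comparison is unbiased. That stands: this is a matter of efficiency.

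The second reply is that baseline BBT is not absent from the analysis, and that the article does not give the parameterization of the longitudinal model. A change contrast or a common baseline mean would use the baseline score. This stands in part. It is wrong to say that the plan ignores baseline BBT. But the article describes a group difference at each time point and names the adjustment set outright, and on that reading the information is not used.

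The third reply is that finger extension may already carry most of what baseline BBT would add, especially if patients without it cannot move blocks. That lowers the gain, as the floor calculation shows, but does not remove it under the settings tried.

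Two stronger readings are tempting and are not supported:

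- **A reader might infer that the primary comparison is underpowered and that this omission is a cause.** The protocol states no SD. If 37 is the paired, within-group size that the text describes, the implied SD of change is 5.5 × √37 / 2.802 = 11.9. Using that as a stand-in for the between-patient SD, 37 per arm has about 51% power for a 5.5-block difference between arms. If 37 came from a two-sample formula, the implied SD is 5.5 × √(37/2) / 2.802 = 8.4 and power is 80%. The documents do not settle which applies, and the basis of the sample size is a separate question. A power gain from adjustment cannot be quoted either, because it needs both an SD and a correlation that are not given.
- **A reader might infer that the primary analysis is left open because two model types are named.** The endpoint and time point are fixed, and the choice of model is commonly left to a statistical analysis plan, which is not shown here.

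**Conclusion.** The point holds as a loss of precision. The stated adjustment set for the 6-month BBT comparison is sex and finger extension, and baseline BBT, collected before allocation, is not named. Its roles as a repeated outcome with a free group effect at each visit and as a predictor in the attrition weights do not make up for this. There is no bias. The variance given up is ρ²: about 9%, 25% or 49% for an assumed partial correlation of 0.3, 0.5 or 0.7, and less if baseline BBT is at its floor in patients without finger extension. The direction is certain for any useful correlation; the size cannot be determined from the protocol.

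**What to change.** State in the Statistical analysis section that the ESS minus sham difference in BBT at 6 months is estimated with adjustment for baseline BBT, sex and finger extension. This can be done by ANCOVA, or by a longitudinal model of the three visits with a common baseline mean in both arms; in the simulation the two were about equally precise (SE 2.40 and 2.41). Adjust each secondary outcome for its own baseline value in the same way. The attrition weights can stay as planned. The cost is one sentence and one model term per outcome, with no new data. Recruitment was still open when the article was submitted, so the article itself shows no obstacle to making the change before analysis.

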We are collecting data on the following variables to characterize the sample and to assess whether the randomization is successful: (a) age, (b) gender, (c) profession, (d) living condition (i.e., married or living with another person, alone), (e) risk factors for stroke: smoking, alcohol consumption, prestroke nutritional habits, prestroke physical activity level, weight, height, Body Mass Index, waist circumference and other risk factors for stroke (e.g., previous stroke, hypertension, hyperlipidemia, heart disease), (f) type of stroke (i.e., hemorrhage or infarction), (g) subtype of ischemic stroke [38], (h) severity of stroke at baseline [39], (i) stroke acute treatment, (j) affected upper limb, (k) dominant hand, (l) medications, (m) complications during hospitalization, (n) amount and content of upper limb training following ESS and (o) amount and content of usual rehabilitation. For further information, see Table 1.

**Table 1 Tab1:** Time schedule of enrollment, intervention, assessments and responsible trial personnel

Trial procedure	Time points during the course of the trial					Responsible personnel	Blinded to group allocation?
	Stroke onset – 7 days post stroke	ESS treatment	Post- intervention	Hospital discharge	6-month follow-up		
Assess eligibility	X					EG	Not applicable
Present trial information for potential participants	X					EG/ESS personnel	Not applicable
Collect informed consent	X					EG	Not applicable
Group allocation	X					Administrative personnel/SPM	No/no
Assess outcome	X		X		X	EG	Yes
Collect sociodemographic data	X			X	X	EG	Yes
Collect medical data	X			X	X	MS/EG/ESS personnel	Yes/yes/no
Collect data on prestroke nutritional habits and physical activity	X					EG/ESS personnel	Yes/no
Collect data on upper limb training and usual rehabilitation		X				OTs or PTs at the stroke unit and in the community	Yes
Collect data on ESS treatment, including adverse events		X				ESS personnel	No

*EG* [name], *ESS* electrical somatosensory stimulation, *MS* [name], *OT* occupational therapist, *PT* physiotherapist, *SPM* [name]

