Designing the control ESS treatment was challenging since the intervention can be perceived by the trial participants who may also interact with each other during hospitalization. Since a completely inactive ESS treatment gave rise to concerns about high dropout rates in the control group, we designed a sham ESS treatment with an extremely low treatment dose. It is unlikely that the total amount of sham ESS treatment (1.2 min) is sufficient to induce any training effects. However, we are unable to verify this since we do not have a trial arm receiving completely inactive or no ESS. As a consequence, our trial results can be biased towards an underestimation of the effect of ESS treatment. It is noteworthy that both the control and the intervention group receive the same amount of attention from the personnel during the ESS sessions. Although some participants might figure out their group allocation, we hope that they would be motivated to continue in the trial due to fact that they are offered upper limb training in addition to the usual rehabilitation.

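### The listed predictors of the attrition weights omit allocated group, so loss that depends on group jointly with prognosis is left uncorrected

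*Protocol article*

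**What the plan says.** The Statistical analysis section of the protocol article gives the weights a purpose: "Possible differential attrition is adjusted for by weighting the outcomes that are available at each of the study time points", using the inverse of the probability of being present. On the model behind the weights it says "these probabilities are estimated in logistic regression models including all background characteristics and outcomes at previous study time points".

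Two places show that allocation is not a background characteristic here. The same section opens with "Background characteristics will be compared between the intervention groups with" *t* tests or chi-squared tests, so these are variables set against group. Under Trial setting and participants, the list introduced by "We are collecting data on the following variables to characterize the sample and to assess whether the randomization is successful" runs from item (a) to item (o) and does not contain allocation.

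The outcome models are to be adjusted for the two stratification variables, sex and finger extension. Baseline BBT is not named as a covariate.

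On whether loss could differ by arm, the Blinding section says that "participants can feel the stimulation and are aware of whether it is delivered in continuous or intermittent sham mode". The Discussion says that "a completely inactive ESS treatment gave rise to concerns about high dropout rates in the control group", and that the low-dose sham was designed in response.

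**The concern.** A presence model without group gives the same weight to a sham and an ESS patient with the same covariates, even if one was much less likely to be seen at six months. Suppose sham patients with poor early recovery leave more often than comparable ESS patients. The remaining sham patients then look too good, and the weights do not restore the missing ones in the right arm. The ESS-versus-sham contrast in six-month BBT, the primary outcome, would be biased while the report describes attrition as adjusted for.

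**Working it through.** **Planned attrition.** Inputs from Sample size estimation: 37 patients before attrition, 8% deaths, 20% other loss, 51 per group.

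- Retention = 0.92 × 0.80 = 0.736, so loss = 26.4%.
- 37 / 0.736 = 50.27, rounded up to 51. The plan's figure is reproduced.
- Expected losses = 0.264 × 102 = 26.9, about 27 in total or 13 per arm.

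**Scale.** No BBT SD is given. Reading 37 as the size of each of two groups compared on a 5.5-block difference (two-sided 5%, 80% power), the normal approximation implies SD = 5.5 × √(37/2) / (1.960 + 0.842) = 8.44 blocks. This is an assumption, because the protocol words its calculation as a within-group improvement. On that reading the same inputs imply an SD of change of 5.5 × √37 / 2.802 = 11.94.

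**Simulation.** 1,000,000 patients, 1:1 allocation, mean retention about 73.6%, no true effect. Finger extension predicts a standardised baseline score X. The post-intervention score is L = 0.8X + noise (SD 0.6), and the six-month score is 0.75L + 0.15X + noise (SD 0.5). Dropout follows a logistic model with log-odds coefficients of 0.8 for L, for group, or for both. The outcome regression contains group and finger extension (sex was not simulated). Bias is the estimate minus the full-data estimate, ESS minus sham, in outcome SDs. The coefficients and dropout models are assumed.

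| Loss depends on | Retained, sham / ESS | No weights | Weights as listed | Group added | Group and group-by-covariate terms added |
|---|---|---|---|---|---|
| Group only | 66.0% / 81.2% | 0.00 | 0.00 | 0.00 | 0.00 |
| L only, same in both arms | 73.6% / 73.6% | 0.00 | 0.00 | 0.00 | 0.00 |
| Group and L, additive | 66.8% / 80.5% | −0.07 | −0.08 | 0.00 | 0.00 |
| L in sham arm only | 72.2% / 74.9% | −0.14 | −0.15 | −0.15 | 0.00 |
| L in sham arm only, plus higher sham loss | 65.2% / 82.0% | −0.18 | −0.19 | −0.14 | 0.00 |
| L in opposite directions by arm | 73.5% / 73.5% | +0.28 | +0.28 | +0.28 | 0.00 |

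The last row is an extreme that nothing in the article points to, and it is not used in the verdict.

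**With a true effect of 0.5** (about half an SD: outcome variance 0.75² + (0.75 × 0.6)² + 0.5² = 1.015), partly acting through L:

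- Loss depending on L only: retention differs by arm (71.6% versus 75.6%). Bias is −0.02 unweighted and 0.00 with the listed weights.
- Additive dependence: −0.09 unweighted, −0.07 with the listed weights, 0.00 once group is added.
- The two sham-only patterns: −0.15 and −0.19 with the listed weights, as before.

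**In blocks, at SD 8.44.** Additive: 0.072 × 8.44 = 0.6 to 0.078 × 8.44 = 0.7. Sham arm only: 0.154 × 8.44 = 1.3 to 0.193 × 8.44 = 1.6.

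**The case against.** The strongest reply is that the text does not strictly exclude group. The predictor list is introduced by the word including, the article condenses a fuller plan that is not shown, and that plan may name group. This limits the point to the published specification. That specification claims all of two named classes of predictor, and group belongs to neither, so an analyst who follows it would leave group out.

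A reader might infer that the weights cannot correct differential attrition at all. The article does not support this. It does not define differential as between-arm. Earlier outcomes are in the model, so arm differences in loss that run through the measured post-intervention score are corrected. Loss that depends on group alone causes no bias.

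A reader might also infer that arm-dependent loss is to be expected. The dropout fear quoted from the Discussion concerned a completely inactive control, which was rejected in favour of the low-dose sham. Attention is equal in both groups, all participants are offered arm training, and they are not told how the stimulation should feel. These measures make arm-dependent loss less likely without ruling it out. The authors themselves only hope that participants who work out their allocation will stay.

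Finally, the sizes depend on assumed slopes and an assumed SD, and a larger SD would give more blocks. In a separate simulation with a single prognostic variable, the bias also vanished when that variable entered the outcome regression. The plan names only sex and finger extension there. Finger extension was already in the regression behind the table, and bias remained.

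**Conclusion.** The concern holds in limited form. As listed, the weight model ignores allocation, so attrition that depends on group jointly with prognosis, beyond the listed covariates, is not corrected. At the planned 26.4% loss the remaining bias is about 0.07 to 0.08 SD for additive dependence and 0.15 to 0.19 SD when prognosis drives loss only in the control arm. With no true effect this is no better than leaving the data unweighted; with a true effect, the weights remove a small part of the additive bias.

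At an assumed SD of 8.44 blocks this is about 0.6 to 1.6 blocks, or 11% to 29% of the 5.5-block target (0.6/5.5 and 1.6/5.5). The direction follows from the assumed pattern, in which sham patients with poor early recovery are lost more often; here it works against ESS. Neither the BBT SD nor dropout by arm is in the article, so these figures illustrate a possible bias and do not predict one. The change is worth making because it costs little.

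**What to change.** State that the presence model for each follow-up visit contains allocated group and its interaction with the last observed BBT score, alongside the earlier outcomes. The interaction is needed because a group main effect repairs only the additive case. In the sham-only patterns it leaves 0.14 to 0.15 SD.

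Group can enter as a masked code, so blinding of the analysts is kept, and no new data are required.

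The cost is one or two extra parameters in a model with about 27 expected losses. The background predictors should therefore be cut to a short prespecified list in place of all fifteen lettered items. Separate full models by arm, with about 13 losses each, would not be stable. Replacing the weights with a likelihood-based longitudinal model is a possible alternative, but it is a trade-off and this point does not require it.

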### Sample size estimation

Using a pretrial power analysis, we determined that a minimum sample size of 37 patients was required for correctly detecting a within-group improvement of 5.5 on the BBT, if such a difference truly exists, with a two-sided significance level of 5% and a power of 80% [51]. The number of 5.5 blocks had previously been reported as the smallest real difference between two measurements for the affected upper limb [41]. Since the minimally clinically important difference on BBT is, to our knowledge, not established yet, we made the assumption that the smallest real difference would be perceived by stroke patients as being of clinical relevance for their daily life. After adjusting for: (a) a case-fatality rate of 8% as reported at 1 year post stroke in a Danish nationwide population-based study [52] and (b) a 20% loss of participants at follow-up for other reasons, we estimated that 51 participants were needed in each group [53]. Hence, the total sample size is 102 participants.

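### The attrition weights are to come from a logistic model with all background characteristics and earlier outcomes, too many parameters for the roughly 27 absences the plan expects at 6 months

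*Protocol article*

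**What the plan says.** The Statistical analysis section weights the outcomes available at each time point by the inverse of the probability of being present, and "these probabilities are estimated in logistic regression models including all background characteristics and outcomes at previous study time points". GEE methods then adjust the variance for the weighting and for repeated observations. The article mentions no selection, penalization, stabilization or truncation.

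The candidate characteristics are listed under Trial setting and participants as fifteen lettered items, (a) to (o). Many are compound: item (e) alone names a dozen risk factors. The list ends with "m) complications during hospitalization, (n) amount and content of upper limb training following ESS and (o) amount and content of usual rehabilitation".

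Outcome measures yields nine scores per visit: Box and Block Test (BBT), Fugl-Meyer, grip strength, three pinch strengths, touch threshold, pain and modified Rankin Scale. Trial design sets three visits, so two precede the primary BBT assessment at 6 months.

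Sample size estimation allows for 8% case fatality and "a 20% loss of participants at follow-up for other reasons", and concludes "Hence, the total sample size is 102 participants".

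**The concern.** In a logistic model for presence, the rarer category limits how many coefficients the data can support, and here that is the absent patients. With too many coefficients one of two things tends to happen. Some patients who stayed get a very low fitted probability, so a handful of large weights dominate the estimate. Or the covariates separate present from absent perfectly, every present patient gets a fitted probability of 1, and the weighted analysis becomes the unweighted one.

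This bears on the primary 6-month comparison. The Blinding section concedes that participants can feel which mode they receive, and the Discussion records worry about dropout in the control group. Weighting is the plan's stated safeguard against differential loss, so a rule that may disable it matters.

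**Working it through.** **1. The plan's own figure.** The evaluable number is 37 per group ("a minimum sample size of 37 patients was required for correctly detecting a within-group improvement of 5.5 on the BBT"). Inflation: 37 / (0.92 × 0.80) = 37 / 0.736 = 50.27, rounded up to 51. This agrees with "we estimated that 51 participants were needed in each group", and 2 × 51 = 102. The 37 itself cannot be checked because no standard deviation is given; nothing below depends on it.

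**2. Expected absences at 6 months.** 102 × (1 − 0.736) = 26.9. Adding the two rates gives 102 × 0.28 = 28.6; subtracting 2 × 37 = 74 from 102 gives 28. About 27 is a fair planning figure.

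**3. Parameters in the 6-month weight model (my count; intercept not counted).**
- Narrowest: items (a) to (l) at one parameter each, plus BBT at two visits: 12 + 2 = 14. With items (m) to (o): 15 + 2 = 17.
- One parameter per lettered item and all nine scores at two visits: 15 + 18 = 33.
- Literal, each named sub-item once: (a) to (d) 4, (e) 12, (f) to (m) 8, (n) and (o) 2 each, total 28; 28 + 18 = 46, before extra terms for multi-category items.

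**4. Absences per parameter.** 26.9/14 = 1.9; 26.9/17 = 1.6; 26.9/33 = 0.8; 26.9/46 = 0.6.

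**5. Consequence, by simulation.** The setting is 102 patients with about 26% absent, main-effects logistic weights and a sandwich standard error. Covariate correlations and absence mechanisms are assumed. Error rate means type I error in the null runs and non-coverage of the 95% interval otherwise. The ratio compares the SD with that of the small model in the same set.

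| Set | Covariates | SD of estimate | Ratio | Error rate | Separated |
|---|---|---|---|---|---|
| Null 1 | 6 | 0.225 | 1 | 6.3% | – |
| | 33 | 0.276 | 1.23 | 9.0% | 3% |
| | 40 | 0.309 | 1.37 | 9.1% | 40% |
| Null 2 | 6 | 0.233 | 1 | 5.8% | – |
| | 17 | 0.238 | 1.02 | 6.1% | – |
| | 33 | 0.276 | 1.18 | 7.4% | – |
| | 40 | 0.321 | 1.38 | 8.8% | – |
| | 50 | 0.254 | 1.09 | 6.6% | – |
| Null 3 | 4–6 | 0.244–0.254 | 1 | 5–6% | – |
| | 17–40 | 0.27–0.28 | 1.06–1.15 | 6–7% | 22% at 33, 65% at 40 |
| Effect 5.5, absence depends on arm and one covariate | 4 | 2.22 | 1 | 5.3% | 0% |
| | 16 | 2.54 | 1.14 | 8.0% | 1% |
| | 25 | 2.75 | 1.24 | 10.3% | 16% |
| | 30 | 2.62 | 1.18 | 10.8% | 44% |
| | 46 | 1.90 | 0.86 | 9.8% | 99% |
| Effect 5.5, absence depends on an arm-by-covariate interaction | 4 | 1.93 | 1 | 7.7% | 0% |
| | 16 | 2.05 | 1.06 | 7.3% | 0% |
| | 30 | 2.39 | 1.24 | 9.2% | 7% |
| | 46 | 2.04 | 1.06 | 8.7% | 90% |

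Separation was also seen in 93% of runs at 46 covariates (Null 3) and 97% at 50 (Null 1).

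The standard error lags behind the true variability. In the first effect set the mean standard error is 2.18 against an SD of 2.54 at 16 covariates (14% too small), and 2.16 against 2.75 at 25 (21% too small).

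The same set shows the adjustment vanishing. At 46 covariates the mean estimate is 4.34 for a true 5.5, identical to the unweighted mean; the small model gives about 5.4. The loss is 5.5 − 4.34 = 1.16 blocks under that assumed mechanism.

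In the interaction set, the 4-covariate model already misses 7.7%, because main-effects weights omit the interaction. Only the rise above that figure reflects model size.

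**The case against.** The strongest reply is that the count is uncertain. The article does not say that its background characteristics are all of items (a) to (o), and earlier outcomes could mean earlier values of the outcome being analysed. At 17 covariates, Null 2 is hardly distinguishable from the small model (6.1% against 5.8%). That stands: 33 is not a minimum, and the harm on the narrow reading may be small. It does not remove the point, since the wording is all-inclusive and even 14 parameters leave under 2 absences each.

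Second, the excess error rate is partly a matter of variance estimation. In Null 1 to 3, an HC3 variance with a t reference gave about 4–5% at every model size tried, and the article does not commit to an uncorrected sandwich. So a reader should not infer that the type I error must exceed 5%. A corrected variance does not, however, restore lost precision or prevent separation.

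Third, the two harms do not peak together: once the model separates, variance inflation largely disappears. This is correct, and is why the point is put as one or the other.

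Fourth, including many dropout predictors makes missing-at-random more plausible. That is a good reason for a rich model when absences are plentiful, which they are not here.

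A reader might also infer that many patients would get no weight because of one missing field, or that ischemic subtype is unusable in hemorrhage. The documents support neither. They give no missingness rate and do not prescribe dropping such patients, and the subtype needs only a category for hemorrhage. These are details for the analysis plan.

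**Conclusion.** The point holds as a should-fix of moderate size. The absence count follows from the plan's own rates, and the model is over-sized on every reading considered. In the simulations the true variability usually grows by about 10–25% (from 2% at 17 covariates to 38% at 40), with error rates of about 6–11% instead of 5%. At about 40–50 parameters separation is usual, reaching 90% or more at 46, and the adjustment is then lost.

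It would go too far to call the primary estimate unreliable. The harm runs from negligible to moderate depending on a count the article does not state.

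Assumptions: 27 is a planning figure, and fewer absences would worsen the ratio. Parameter counts are inferred. Correlations and absence mechanisms are invented, and separation rates differ between sets accordingly (3% or 22% at 33 covariates). The two effect sets did not adjust the outcome regression for sex and finger extension, as the plan will. An unseen analysis plan may shorten the list; if so, it departs from the published rule and should say so.

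**What to change.** Replace the all-inclusive rule by a short, named list of variables measured before the time point being weighted. An example is arm, sex, finger extension, age, baseline stroke severity, baseline BBT and, for the 6-month weight, post-intervention BBT. The timing condition matters because items (m) to (o) arise after baseline, and the Intervention section defines usual rehabilitation over the whole six months of participation.

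Add stabilized or truncated weights, and a small-sample-corrected variance or a bootstrap that re-estimates the weights. A larger weight model can be kept as a sensitivity analysis. Moving the primary analysis to a likelihood-based model or multiple imputation would be a preference and is not needed to resolve this point.

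The cost is wording and programming, settled before unblinding. The small downside is that dropout predictors outside the list are not used in the primary weights.
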